## Secondary Efficacy Analyses

The secondary efficacy analyses will extend the evaluation of short-term memory suppression and further explore long-term effects, subgroup differences, and comparisons across emotional valence.

1. Long-Term Memory Suppression Analysis

The primary endpoint analysis conducted on Day 1 will be repeated on Day 2 (24 hours post-gaming) and Day 4 (72 hours post-gaming). This will determine whether the suppression effects observed (Conscious < Control, Unconscious < Control) persist over time, indicating long-term memory suppression.

1. Time-Based Changes in Memory Performance

To assess how memory performance changes over time for each subgroup (control, treatment, conscious, unconscious), a Difference-in-Difference (DID) analysis will be conducted. This analysis will be adjusted for the following covariates:

- Total duration of the self-feedback process during the Learning phase.
- Repetition frequency of each image during the Learning phase.

1. Emotional Valence Comparisons

To examine the differences between negative and positive emotional valence at each timepoint (Day 1, Day 2, Day 4), paired two-tailed t-tests will be performed. The comparisons will include:

- Negative Treatment vs Positive Treatment
- Negative Conscious vs Positive Conscious
- Negative Unconscious vs Positive Unconscious
- Negative Conscious vs Positive Unconscious
- Negative Unconscious vs Positive Conscious

These analyses will evaluate whether emotional valence influences memory suppression and whether differences between groups change over time.

To support these comparisons, descriptive statistics (mean, standard deviation, t statistics, coefficient estimates, p-values) will be calculated. The summary statistics and results for the secondary efficacy analyses will be produced in accordance with Section 8 of this SAP.

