## Endpoints

(ICH E9; 2.2.2)

1. Primary Endpoint

- Endpoint: Short-term memory suppression (METEOR scores).
- Definition: Memory suppression will be assessed using METEOR scores, a measure of semantic similarity reflecting accurate and context-rich recall.
- Time Point: Day 1 (immediately post-intervention).
- Comparisons:
- Cue exposure conditions: Conscious vs Control, Unconscious vs Control.
- Subgroup analysis: Positive vs Negative emotional valence.
- Hypothesis:
- Total Image Group: Conscious < Control, Unconscious < Control (one-tailed t-test).
- Negative Image Group: Conscious < Control, Unconscious < Control (one-tailed t-test).
- Positive Image Group: Conscious < Control, Unconscious < Control (one-tailed t-test).

2. Secondary Endpoints

- Endpoint 1: Long-term memory suppression (METEOR scores over time).
- Definition: Assessment of METEOR scores on Day 2 (24 hours post-intervention) and Day 4 (72 hours post-intervention) to evaluate memory suppression persistence.
- Time Points: Day 1, Day 2, Day 4.
- Analysis: Repeated paired t-tests (Conscious vs Control, Unconscious vs Control).
- Endpoint 2: Group differences in memory performance trajectories.
- Definition: Evaluation of memory decline over time using Difference-in-Differences (DID) analysis, adjusted for covariates such as: feedback Cycle Times (duration of self-feedback process during the learning phase), and frequency of Image Repetition (number of image viewings during the learning phase).
- Purpose: To supplement time-specific t-test comparisons and better understand group differences in forgetting trajectories.
- Endpoint 3: Emotional valence-based comparisons.
- Definition: Paired two-tailed t-tests comparing METEOR scores across valence conditions at each time point:
- Negative Treatment vs Positive Treatment
- Negative Conscious vs Positive Conscious.
- Negative Unconscious vs Positive Unconscious.
- Negative Conscious vs Positive Unconscious.
- Negative Unconscious vs Positive Conscious.

3. Exploratory Endpoints

- Endpoint: EEG-based neural activity analysis.
- Definition: Neural activity will be compared across cue exposure conditions and emotional valence groups using EEG power spectrum density.
- Frequency Bands: Alpha, beta, theta, delta, and gamma.
- Comparisons:
- Cue Exposure: Conscious vs Unconscious phases.
- Emotional Valence: Negative vs Positive image groups.
- Statistical Method: Two-tailed Wilcoxon signed-rank test for paired comparisons.

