## Exploratory Efficacy Analyses

The exploratory efficacy analysis will evaluate differences in neural activity (EEG data) across two comparisons:

1. Cue Exposure Condition: Neural activity during the Conscious phase will be compared to the Unconscious phase, regardless of emotional valence.
2. Emotional Valence: Neural activity for Negative images will be compared to Positive images, regardless of cue exposure condition.

To minimize individual variability, EEG segments will be paired within participants:

- For cue exposure comparisons, the i-th EEG segment from the Conscious phase will be paired with the corresponding i-th segment from the Unconscious phase.
- For emotional valence comparisons, EEG segments from Negative and Positive image groups will be paired for the same participant.

Statistical significance will be assessed using two-sided Wilcoxon signed-rank tests for each set of paired comparisons. To support these comparisons, descriptive statistics (median value of power spectral density for each channel and frequency band, W statistics, p-values) will be calculated. The summary statistics and results will be reported in accordance with Section 9 of this SAP.

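### Two of the five contrasts in the valence endpoint change exposure and valence together, so an exposure difference could be reported as a valence effect or could hide one

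*SAP*

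**What the plan says.** SAP section 4.2 (Endpoints) defines secondary Endpoint 3 as "Paired two-tailed t-tests comparing METEOR scores across valence conditions at each time point". Section 9.2 (Secondary Efficacy Analyses) repeats the plan: "To examine the differences between negative and positive emotional valence at each timepoint (Day 1, Day 2, Day 4), paired two-tailed t-tests will be performed". Both sections give the same five contrasts. Three set negative against positive images within the same exposure: Treatment, Conscious and Unconscious. The remaining two are "Negative Conscious vs Positive Unconscious" and "Negative Unconscious vs Positive Conscious". Section 9.2 then states what the set is for: "These analyses will evaluate whether emotional valence influences memory suppression and whether differences between groups change over time".

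For exposure, the recall comparisons named for the primary endpoint in section 4.2 are "Cue exposure conditions: Conscious vs Control, Unconscious vs Control", and the same pairs are repeated on Day 2 and Day 4. A direct comparison of the two active exposures is named only for EEG, in section 9.3: "Neural activity during the Conscious phase will be compared to the Unconscious phase, regardless of emotional valence".

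**The concern.** A contrast can be read as a valence effect only if valence is the one thing that differs between its two sides. In the two crossed contrasts the exposure condition differs too. Any difference in recall between conscious and unconscious cueing then enters the result at full size, and a single crossed test cannot separate it from valence. The SAP nevertheless lists these tests under the valence endpoint and says that the set will show whether valence matters.

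What is at stake is the conclusion of a secondary endpoint. A pure exposure difference could be taken for emotional modulation. Equally, a true valence effect could be cancelled in one of the two contrasts by an exposure difference of similar size.

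**Working it through.** The SAP states no effect size, standard deviation or power for these tests, so there is no figure of its own to reproduce. The check has two parts.

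**1. What each contrast estimates.** Write NC, NU, PC and PU for the mean METEOR scores of negative/positive images under Conscious/Unconscious cueing. Take Treatment as the average of Conscious and Unconscious (an assumption; the SAP does not define it). Define:

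- V = (NC + NU)/2 − (PC + PU)/2, the valence effect on recall
- E = (NC + PC)/2 − (NU + PU)/2, the Conscious-minus-Unconscious effect
- I = [(NC − PC) − (NU − PU)]/2, the interaction of the two

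| Contrast | Estimates |
|---|---|
| Negative vs Positive Treatment | V |
| NC − PC | V + I |
| NU − PU | V − I |
| NC − PU | V + E |
| NU − PC | V − E |

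For example, V + E = (NC + NU − PC − PU + NC + PC − NU − PU)/2 = NC − PU.

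The first three contrasts contain no E. The last two carry all of E, with opposite signs. They also contain no I, so they do not bear on the third objective in section 4.1, which asks whether exposure effects differ by valence. If V = E, then NU − PC = 0 and a real valence effect disappears from that test.

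**2. How often a crossed test rejects when valence has no effect.** Inputs:

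- n = 150 (section 6).
- Paired t-test at 5% (section 9), two-tailed (section 9.2).
- V = 0.
- dz = E divided by the SD of the paired difference. This is not in the SAP, so it is varied from 0 to 0.3.

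The statistic follows a noncentral t with 149 degrees of freedom and noncentrality dz·√150; the critical value is 1.976. At dz = 0.2 the noncentrality is 0.2 × 12.25 = 2.45.

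| Assumed dz | Rejection probability, each crossed test |
|---|---|
| 0 | 0.05 |
| 0.1 | 0.23 |
| 0.2 | 0.68 |
| 0.3 | 0.95 |

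A simulation of 20,000 runs, with equal cell SDs and an assumed within-subject correlation of 0.5, agrees. At dz = 0.2 the crossed tests reject in 0.685 and 0.681 of runs, while the three same-exposure tests stay at 0.048 to 0.050. At least one crossed test rejects in 0.899 of runs, so both reject in 0.685 + 0.681 − 0.899 = 0.467.

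**Extent.** 2 crossed contrasts × 3 timepoints = 6 of the 5 × 3 = 15 valence tests.

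**The case against.** The best defence is that a careful reader would not be misled. Each contrast is named by its two cells, so the change of exposure is visible. Three clean contrasts stand in the same list. If there were an exposure difference and no valence effect, those three would stay near 5% while the crossed pair leaned in opposite directions, which does not look like valence. The closing sentence of section 9.2 covers all five tests and change over time; it does not say that a crossed result alone settles the matter. Half the sum of the two crossed contrasts even equals V, and half their difference equals E.

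Part of this stands. The harm depends on E, which the SAP does not give; if E = 0, both crossed contrasts are valid valence tests. But the SAP sets no rule for reading the five tests jointly and plans neither the half-sum nor the half-difference. It treats the two exposures as distinct conditions throughout and gives no ground for assuming E = 0.

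A reader might also infer that the plan omits a required analysis, because no recall test of Conscious against Unconscious is named. The documents do not support that. The first objective in section 4.1 and the a priori hypothesis in section 7.3 are both against Control. The preface's aim of verifying both presentations can be met by two such tests, and an EEG contrast does not oblige a recall contrast. Nor is the comparison excluded: the difference-in-differences analysis lists both exposures as subgroups without naming a reference, and section 4.3 gives its group comparisons only as examples.

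**Conclusion.** The point holds in a conditional form. Two of the five contrasts listed under the valence endpoint are mixed exposure-and-valence contrasts. If Conscious and Unconscious recall differ, they could yield a false valence finding or mask a true one. At n = 150 with no valence effect, each rejects with probability between 0.05 (dz = 0) and 0.95 (dz = 0.3). These rates rest on assumed values of dz, not on anything in the SAP. The decomposition into V+E and V−E needs no such assumption.

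A reader might go further and say that an exposure difference will make both crossed tests significant. The arithmetic does not bear that out: at dz = 0.2 both reject together in slightly under half of trials.

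The consequence is confined to 6 of 15 secondary tests. The primary Day 1 tests, the long-term tests against Control and the three same-exposure valence contrasts are untouched. It is a moderate fault, worth correcting because the correction is nearly free.

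**What to change.** In sections 4.2 (Endpoint 3) and 9.2, do one of the following:

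- delete the two crossed contrasts from the valence comparisons, which leaves 3 × 3 = 9 tests; or
- keep them, labelled as mixed exposure-and-valence contrasts, and state that no valence conclusion will be drawn from them.

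In either case, state that the valence conclusion rests on the three same-exposure contrasts.

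Optionally, if the sponsor wants to compare the two presentations on recall, add a two-sided paired Conscious vs Unconscious METEOR comparison. It should stand under a separate exposure heading, not inside the valence endpoint, and be labelled exploratory. Report it as an estimate with a confidence interval, and do not read a non-significant result as evidence that the two presentations work equally well.

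The cost is a change of wording, with no new data. The two crossed results are no longer available as valence tests.

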# Study Objectives and Endpoints

## Study Objectives

(ICH E3; 8.)

The purpose of this study is to evaluate the effects of cue exposure conditions (Conscious, Unconscious, Control) on short-term and long-term memory suppression and to determine whether these effects are modulated by emotional valence (Positive, Negative).

Specifically, this study aims to:

1. Short-Term Effects: Assess the immediate impact of conscious and unconscious cue exposure on memory suppression compared to a control condition, using METEOR scores measured immediately after the intervention (Day 1).
2. Long-Term Effects: Investigate whether the suppression observed on Day 1 persists over time (Day 2, Day 4), reflecting long-term forgetting trajectories across exposure conditions.
3. Interaction with Emotional Valence: Determine whether the effects of cue exposure conditions differ for images with positive versus negative emotional valence, highlighting potential emotional modulation of memory suppression processes.
4. Neural Correlates: Explore the underlying neural mechanisms of memory suppression by analyzing EEG activity, focusing on comparisons between exposure conditions (Conscious vs. Unconscious) and valence (Negative vs. Positive) across key frequency bands (alpha, beta, theta, delta, gamma).

This comprehensive approach will provide insights into both the behavioral and neural dimensions of memory suppression, offering a deeper understanding of how cue exposure and emotional content influence forgetting processes.

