**2. Subgroups**

Subgroup analyses will be conducted to evaluate the interaction effects between the following variables:

- **Exposure Condition:**
  - Control, Conscious, Unconscious.
- **Emotional Valence:**
  - Positive, Negative.

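### The valence comparisons leave out Control, so they mix a general recall difference between negative and positive images with any difference in suppression, and objective 3 has no valid formal test

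*SAP*

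**What the plan says.** **The question.** Objective 3 in SAP section 4.1 is to "Determine whether the effects of cue exposure conditions differ for images with positive versus negative emotional valence". That is an exposure-by-valence interaction. Section 7.3 uses the word itself: "Subgroup analyses will be conducted to evaluate the interaction effects between the following variables", followed by exposure condition and emotional valence. It names no model, contrast or test.

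**What suppression means.** Section 9.2 states the "suppression effects observed (Conscious < Control, Unconscious < Control", so suppression is a treated score below the Control score.

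**The tests.** Secondary Endpoint 3 in section 4.2 specifies "Paired two-tailed t-tests comparing METEOR scores across valence conditions at each time point". The list in section 9.2 opens with "Negative Treatment vs Positive Treatment". It continues with negative against positive within Conscious and within Unconscious, then two crossed pairs: negative Conscious with positive Unconscious, and negative Unconscious with positive Conscious. The outcome is the METEOR score itself, not its difference from Control.

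**The conclusion to be drawn.** "These analyses will evaluate whether emotional valence influences memory suppression and whether differences between groups change over time".

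**The concern.** The objective is about a difference between two effects, each measured against Control. The planned tests compare two treated means. If negative and positive images are recalled unequally well even when no cue is shown, that inequality passes straight into every one of the five comparisons, where it can be read as valence altering suppression. It can equally cancel a real difference in suppression and leave the treated means alike.

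The stake is one of four numbered objectives. Section 3.1 motivates the study by the weakening of traumatic memories, so a statement that negative memories are suppressed more, or less, than positive ones would draw attention. The planned tests could not support it.

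**Working it through.** **Inputs from the SAP.** 150 participants, within-subject (sections 5.1 and 6); paired two-sided tests at each of three days (section 9.2); 5% level (section 9). The SAP gives no figure for the valence analysis, so there is none to reproduce.

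**Inputs assumed.** Equal SD of 1 in every exposure-by-valence cell, a common within-person correlation ρ between cells of 0 to 0.7, and a valence gap in Control recall of 0.1 to 0.4 cell SD.

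**Step 1: what the contrast estimates.** Put suppression = Control − Treated, so Treated = Control − suppression. Then

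NegTreated − PosTreated = (NegControl − PosControl) − (NegSuppression − PosSuppression).

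The first bracket is the general recall gap; the second, with its sign reversed, is what objective 3 asks about. The contrast isolates the second only when the first is zero. In a crossed pair the second bracket becomes, for example, NegSuppression under Conscious minus PosSuppression under Unconscious, so valence and exposure change together.

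**Step 2: whether another analysis supplies the missing contrast.**
- Section 9.1 tests each treated condition against Control separately within negative and within positive images. It does not compare the two effects; significance in one valence and not in the other is not a test that they differ.
- The difference-in-differences in section 9.2 is over time (Tables 5.1 and 5.2 in section 16: Day 1 to Day 2 and Day 2 to Day 4), not between valences.
- Section 4.3 derives Control-versus-treated differences but does not compare them across valence.
- Section 7.3 states an intention without a method.

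**Step 3: variances.** The raw difference has variance 2(1 − ρ). The Control-subtracted contrast (NegControl − NegTreated) − (PosControl − PosTreated) has variance 4(1 − ρ), twice as large.

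**Step 4: false signals.** Suppression is equal in both valences and the recall gap is g. The noncentrality of the paired t-test is g√150 / √(2(1 − ρ)); for g = 0.3 and ρ = 0 it is 0.3 × 12.247 / 1.414 = 2.60. Rejection rates of the planned raw test:

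| Gap (cell SD) | ρ = 0 | ρ = 0.3 | ρ = 0.5 | ρ = 0.7 |
|---|---|---|---|---|
| 0.1 | 14% | 18% | 23% | 35% |
| 0.2 | 41% | 54% | 68% | 88% |
| 0.3 | 73% | 87% | 95% | 99.7% |

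The Control-subtracted contrast rejects in 5% throughout, because its expectation is zero whatever g is.

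**Step 5: masked signals.** Suppression of 0.4 occurs only in negatives, and negatives are recalled 0.4 better under Control. The treated means are then equal, and the raw test rejects in 5%. The Control-subtracted contrast has noncentrality 0.4√150 / √(4(1 − ρ)), which at ρ = 0 is 0.4 × 12.247 / 2 = 2.45. Its power is 68%, 83%, 93% and 99% at ρ = 0, 0.3, 0.5 and 0.7.

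**Step 6: simulation check.** 20,000 trials per scenario, ρ = 0.5. A gap of 0.3 with equal suppression gave raw 95.4%, Control-subtracted 5.0%. Suppression of 0.3 in negatives only, with equal treated means, gave 5.0% and 73%. No gap and equal suppression gave about 5% for both.

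**The case against.** **The raw contrast is not blind to suppression.** A reader might infer that the five tests measure only which images are better remembered. Step 1 does not support that: a suppression difference does enter the contrast. If Control recall were equal across valences, the same-condition comparisons would be valid and more precise than the interaction contrast. How images were chosen or matched may be in the protocol, which is not at hand, so the actual gap is unknown. This stands as a limit on the wording, but the SAP neither relies on such equality nor tests it.

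**Objective 3 is not ignored.** Sections 9 and 9.1 report means and SDs by exposure and valence, Control included, so a gap would be visible. The Control-referenced tests are run within each valence and repeated on Days 2 and 4. Table 5 appears to run the difference-in-differences within each valence as well. It would therefore go too far to say that the plan leaves the objective unaddressed. What is missing is a formal test of it.

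**The concluding sentence is loosely placed.** Its second half, on change over time, fits the difference-in-differences better than separate tests at each day, so it may refer to the whole of section 9.2. That softens the quotation but supplies no contrast.

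**The illustration depends on assumptions.** The rates move with the unit of the gap, with ρ and with N. Section 5.2 excludes participants outside the interquartile range of feedback times, which read literally could remove about half, whereas section 8.2 keeps them in the Full Analysis Population. With 75 participants and ρ = 0.5, the rates in Step 4 would be 14%, 40% and 73%. This stands, and it is why ranges are given.

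**The reach is limited.** This is a secondary endpoint, and the primary comparisons with Control are unaffected.

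**Conclusion.** The point holds in this form: the same-condition valence tests confound the Control recall gap with the suppression difference, the crossed tests further confound valence with exposure, and no other section specifies a formal exposure-by-valence test. As written, objective 3 has no valid formal test, and section 9.2 commits to a conclusion that its tests cannot carry.

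This rests on the algebra in Step 1 and the plan's own definition of suppression, not on any assumed number. The rejection rates only illustrate what could follow at plausible gaps; they assume equal cell SDs, a common correlation and 150 analysed participants. The documents do not show that a recall gap exists or how large it is, so it cannot be said that the planned tests will mislead, only that they can, in either direction. Nor do the documents require that the crossed comparisons be removed: they are hard to interpret, but harmless if marked as descriptive.

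**What to change.** In section 9.2 and in Secondary Endpoint 3 (section 4.2), name the test for objective 3. At each day, compute within participant (Control − Conscious) for negative images minus (Control − Conscious) for positive images; do the same for Unconscious and for the two pooled as Treatment. Test each two-sided with a paired t-test and report the estimate with a 95% CI. The exposure-by-valence term of a mixed model would serve equally. Refer to this test from section 7.3 and give it a row in the table list of section 16.

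Keep the raw same-condition comparisons only as descriptive. Either label the two crossed comparisons in the same way or drop them. State that no conclusion about suppression will be drawn from any of the five.

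**Cost.** A change of SAP wording; the data are already collected under the plan. The single-condition contrast has about twice the variance of the raw difference under equal correlations, so its interval is about √2 ≈ 1.4 times as wide. With 150 participants, its power for a true suppression difference of 0.3 cell SD is 59%, 73% and 92% at ρ = 0.3, 0.5 and 0.7, so a non-significant result should be read from its interval and not as evidence that valence has no effect.

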# Study Methods

## General Study Design and Plan

(ICH E3;9)

This study employs a **within-subject design**, where each participant serves as their own control. This design reduces inter-subject variability, allowing for more precise comparisons across conditions. The study evaluates the interaction between the following three factors, with participants learning a total of 36 cue-target image pairs, categorized as follows:

- **Exposure Condition:** Control, Conscious, Unconscious
- **Valence:** Positive, Negative
- **Test Timepoint:** Day 1 (immediately post-Gaming), Day 2 (24 hours post-Gaming), Day 4 (72 hours post-Gaming)

This factorial design facilitates the assessment of how exposure condition, emotional valence, and time influence memory performance (measured by METEOR scores) and neural activity (assessed through EEG). The within-subject approach ensures that each participant’s performance under one condition can be directly compared to their performance under other conditions.

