# Listing of Tables, Listings and Figures

| **Table Title** | **Number** | **Population** | **Endpoint** | **Time Points or how to conglomerate** | **Covariates or Subgroups** | **Summary Statistics** | **Formal Analysis** | **Foot Notes** | |  |
| --- | --- | --- | --- | --- | --- | --- | --- | --- | --- | --- |
| Disposition | 1 | NA | Disposition | enroll-day4 | Treatment | count | NA |  | |  |
| Summary of Demographic Variable | 2 | Full Analysis | Age | Baseline | Treatment | n, mean, SD | NA |  | |  |
|  |  |  | Gender | Baseline | Treatment | p% (x/n) | NA |  | |  |
|  |  |  | Corrected Vision | Baseline | Treatment | n, mean, SD | NA |  | |  |
| Summary of scores (METEOR, Gist) | 3.1 | Full Analysis | METEOR scores | Day1 | Full(Treatment, Conscious, Unconscious), Negative(Treatment, Conscious, Unconscious), Positive(Treatment, Conscious, Unconscious) | n, mean, SD | NA |  | |  |
|  |  | Full Analysis | Gist scores | Day1 | As above | n, mean, SD | NA |  | |  |
|  | 3.2 | Full Analysis | METEOR scores | Day2 | As above | n, mean, SD | NA |  | |  |
|  |  | Full Analysis | Gist scores | Day2 | As above | n, mean, SD | NA |  | |  |
|  | 3.3 | Full Analysis | METEOR scores | Day4 | As above | n, mean, SD | NA |  | |  |
|  |  | Full Analysis | Gist scores | Day4 | As above | n, mean, SD | NA |  | |  |
| ShIF in short-term (paired t test) | 4.1 | Full Analysis | METEOR scores | Day1 | As above | n, mean, t statistics, p | NA |  | |  |
|  |  | Full Analysis | Gist scores | Day1 | As above | n, mean, t statistics, p | NA | | |  |
| ShIF in long-term (paired t test) | 4.2 | Full Analysis | METEOR scores | Day2-Day4 | As above | n, mean, t statistics, p | NA | | |  |
|  |  | Full Analysis | Gist scores | Day2-Day4 | As above | n, mean, t statistics, p | NA | | |  |
| DID analysis | 5.1 | Full Analysis | METEOR scores | Day1-Day2, Day2-Day4 | As above | Estimate, standard error, p | NA | |  |  |
|  | 5.2 | Full Analysis | Gist scores | Day1-Day2, Day2-Day4 | As above | Estimate, standard error, p | NA | |  |  |
| The difference in the Power Spectrum Density between “conscious and unconscious” | 6.1 | Full Analysis | PSD values | Day1 | Comparison (Conscious - Unconscious) | PSD, W statistics, p | NA | |  |  |
| The difference in the Power Spectrum Density between “positive and negative” | 6.1 | Full Analysis | PSD values | Day1 | Comparison (Positive - Negative) | PSD, W statistics, p | NA | |  |  |

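### Section 9.2 says the valence comparisons will show whether differences change over time, but no planned analysis tests change in the negative-versus-positive difference

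*SAP*

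**What the plan says.** Section 9.2, item 3 (Emotional Valence Comparisons) lists five negative-versus-positive comparisons of METEOR scores. The method is that "at each timepoint (Day 1, Day 2, Day 4), paired two-tailed t-tests will be performed". The item closes: "These analyses will evaluate whether emotional valence influences memory suppression and whether differences between groups change over time".

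Section 4.2, secondary Endpoint 3, has the same method and nothing further: "Paired two-tailed t-tests comparing METEOR scores across valence conditions at each time point".

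Change over time is handled in item 2 of Section 9.2: "To assess how memory performance changes over time for each subgroup (control, treatment, conscious, unconscious), a Difference-in-Difference (DID) analysis will be conducted". The matching row in Section 16 reads "DID analysis | 5.1 | Full Analysis | METEOR scores | Day1-Day2, Day2-Day4 | As above". Its last cell points back to a list of Treatment, Conscious and Unconscious under each of Full, Negative and Positive images.

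Section 5.1 describes the design in wider terms: "The study evaluates the interaction between the following three factors", the three being exposure condition, valence and test timepoint.

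**The concern.** A paired t-test on one day compares that day's mean difference with zero. Three such tests on three days contain no comparison between days. A difference that is significant on Day 1 and not on Day 4 has not been shown to shrink, and a difference that is significant on both days has not been shown to be stable.

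The closing sentence of item 3 nevertheless presents change over time as something these analyses will evaluate. For the valence difference, the planned output leaves two routes to such a statement: setting the daily p-values side by side, or inspecting the means without an interval for the change. The first can make a stable effect look as if it varies and can hide a real change. The second gives no measure of uncertainty. At stake is a secondary conclusion on whether a valence difference in memory persists or fades between Day 1 and Day 4.

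**Working it through.** **Step 1. Which planned analysis tests which change?**

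| Place in the SAP | What is compared | Tests change in the negative-versus-positive difference? |
|---|---|---|
| 9.2 item 3; 4.2 Endpoint 3 | Negative with positive, one day at a time | No |
| 9.2 item 2 (DID) | Exposure groups over time | No |
| 16, Tables 5.1 and 5.2 | DID for "Day1-Day2, Day2-Day4", at most repeated within negative and within positive images | No; the two valences are not set against each other |
| 16, Figure 6.3 (valence over time) | Means only, whereas Figure 6.2 (exposure over time) also lists DID estimates | No |
| 7.3, Subgroups | Exposure by valence; neither time nor a model is named | No |

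The gap is specific to valence. Change in exposure differences is covered by the DID.

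**Step 2. Inputs for the size.** From the SAP: 150 participants (Section 6), paired two-sided tests, 5% level (Section 9). Section 6 gives no effect size, SD or power, so there is no planned figure to reproduce. Assumed here: each participant's negative-minus-positive difference is normal with SD 1 on each day, everyone is scored on all three days, and the daily differences correlate at ρ = 0.3 to 0.9.

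**Step 3. Power of one daily test.** With true difference d in SD units, t is noncentral with parameter d√150 and 149 degrees of freedom. This gives 50% power at d = 0.161, 80% at d = 0.230 and 95% at d = 0.30.

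**Step 4. Constant difference on all three days.** Simulation, 20,000 trials per setting. Entries are the share of trials in which some days are significant and others are not.

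| True difference (SD) | ρ = 0.3 | ρ = 0.5 | ρ = 0.7 | ρ = 0.9 |
|---|---|---|---|---|
| 0.161 | 60% | 50% | 38% | 22% |
| 0.230 | 40% | 34% | 26% | 15% |
| 0.30 | 12% | 10% | 8% | 5% |

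A direct paired t-test of Day 4 minus Day 1 rejects in about 5% of these trials, as it should.

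**Step 5. Difference that halves, 0.6 SD on Day 1 to 0.3 SD on Day 4.** The Day 1 test is almost always significant and the Day 4 test has 95% power, so both are significant in about 95% of trials at every ρ. For the direct test, the SD of the within-person change is √(2(1 − ρ)), so the standardised change is 0.3/√(2(1 − ρ)).

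| ρ | Standardised change | Power of direct test |
|---|---|---|
| 0.3 | 0.3/√1.4 = 0.254 | 87% |
| 0.5 | 0.3/√1.0 = 0.300 | about 95–96% |
| 0.7 | 0.3/√0.6 = 0.387 | 99.6–99.7% |
| 0.9 | 0.3/√0.2 = 0.671 | 100% |

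**The case against.** The best defence is that the closing sentence speaks of differences between groups, not between valences. Section 4.3 uses almost the same phrase for Control against Conscious or Unconscious. Section 4.2, Endpoint 2, gives group trajectories to the DID as a supplement to the time-specific t-tests. The next paragraph of Section 9.2 mentions coefficient estimates, which t-tests do not produce. On that reading the sentence covers all of Section 9.2 and the DID answers much of it. This stands in part: a reader might infer that the SAP has no test of change at all, and that would be wrong. It does not rescue the valence difference. The sentence closes the valence item and opens with valence, and the DID contrasts exposure groups. Separate DIDs within each valence would again be two results without a comparison between them. The SAP gives no DID equation, so this description rests on its listed groups and table rows.

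Three other strong readings also go too far:

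- **That following the plan produces wrong answers.** The SAP has no rule for inferring change from which days are significant. It also reports means by condition, valence and day and plots them, so a halved difference could be seen. The risk is an unsupported conclusion, not a prescribed one.
- **That mixed daily results are usual.** They are common only for small differences; at 0.30 SD they fall to about 5–12%. The two kinds of error also arise largely in different effect ranges.
- **That every participant supplies complete pairs.** Scores are paired by design, but the Full Analysis Population (7.2.1) needs only one valid score, and missing scores are not imputed (7.4).

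**Conclusion.** The concern holds for the valence difference. Section 9.2, item 3, states an aim of evaluating change over time, its tests are confined to single days, and no other planned analysis compares the negative-versus-positive difference between days.

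The percentages in the working show that the consequence can be material. They depend on assumed effect sizes and correlations, on normality and on 150 fully scored participants. They illustrate a risk and do not predict this trial's results.

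The point concerns a secondary endpoint. It does not extend to change in exposure differences or to the Day 1 primary analysis.

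**What to change.** In Section 9.2, item 3:

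1. Keep the per-day tests, labelled as descriptions of each day.
2. For each same-condition contrast (Treatment, Conscious, Unconscious), compute each participant's negative-minus-positive METEOR difference per day. Test Day 4 minus Day 1, and Day 2 minus Day 1, with a two-sided paired t-test. Report the mean change with its 95% CI in participants scored on both days.
3. For any statement about suppression, use the Control-adjusted contrast: (cued minus Control, negative images) minus (cued minus Control, positive images), compared across days in the same way. Without Control, the contrast in step 2 cannot separate ordinary valence-related forgetting from suppression.
4. State that claims of change in valence differences rest on these contrasts only, and add a table to Section 16.

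If the sponsor does not want these tests, the alternative is to limit the closing sentence to description at each timepoint.

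The cost is SAP wording and one table from scores already collected. Step 2 adds 3 × 2 = 6 secondary tests to the 5 × 3 = 15 planned valence tests, and step 3 adds up to 6 more. Participants not scored on both days drop out of the change contrasts. The power figures above do not carry over to the Control-adjusted contrast, whose SD the SAP does not give.
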